## Abstract

**Background:**

Many studies have already reported encouraging results in the prophylactic therapy of migraine by acupuncture, but there seems to be a lack of high quality randomized controlled trials from China. We design and perform a randomized controlled clinical trial to evaluate the efficacy of acupuncture compared with flunarizine in the prophylactic therapy of patients with migraine without aura in China.

**Methods:**

This trial is a multicenter, prospective, randomized controlled clinical trial. The 140 migraine patients are randomly allocated to two different groups. The acupuncture groups (n = 70) is treated with acupuncture and placebo medicine; while the control group (n = 70) is treated with sham acupuncture and medicine (Flunarizine). Both Flunarizine and placebo are taken 10 mg once per night for the first 2 weeks and then 5 mg once per night for the next 2 weeks. Patients in both groups receive 12 sessions of verum/sham acupuncture in 4 weeks.

**Discussion:**

The study design and the long term clinical practice of acupuncturists guarantee a high external validity for the results. The results of our trial will be helpful to supply the evidence on the efficacy of acupuncture for migraine prophylaxis in China.

**Trial Registration:**

The trial is registered at Controlled Clinical Trials: ISRCTN49839714.

## Background

Migraine leads to recurrent attacks of mostly unilateral, pulsating headache with associated symptoms such as photophobia, phonophobia, nausea, and vomiting. The diagnosis of migraine is based on criteria developed by the International Headache Society in 1988 and revised in 2004 – the International Classification of Headache Disorders II (ICHD II) [1]. Migraine prevalence are roughly 12% of the adults in western countries [2] and 4.2%–14.6% in China [3]. Epidemiological studies from several countries showed that the prevalence of migraine was 16–18% in women and 6–8% in men [4,5]. Approximately 90% of the migraine patients have moderate or severe pain, three quarters have a reduced ability to function during the headache attacks, and one-third require bed rest during their attacks [6].

Some patients with migraine are able to identify headache triggers. Triggers may be inconsistent or additive and are not specific to migraine. For example, menses is a trigger for 60% of female migraine patients. Stress or "let-down" after a stressful event, change in meal schedules or insomnia, and such environmental factors as loud noise, odors, or flickering lights may also precipitate migraine headache [7].

Migraine headache has a complex pathophysiology. Both vascular and neuronal mechanisms have been proposed. Although the mechanisms haven't been exactly known yet, several medications have been given to alleviate pain of patients. Pharmacotherapy can be abortive or prophylactic, and patients who experience frequent, severe headaches often require both approaches. Abortive medications used more than 2 days a week on a regular basis may lead to chronic daily or rebound headaches, so patients with headaches symptoms more than a few days a week should be on headache prophylactic therapy [7]. The goals of migraine prophylactic therapy are to (1) reduce attack frequency, severity, and duration, (2) improve responsiveness to treatment of acute attacks, and (3) improve function and reduce disability. Additional goals are to reduce costs and possibly prevent progression of episodic to chronic migraine. Prophylactic medication groups include β-adrenergic blockers, antidepressants, calcium-channel antagonists, serotonin antagonists, anticonvulsants, nonsteroidal anti-inflammatory drugs, and others (vitamins, minerals, natural products) [8]. Calcium-channel antagonists such as flunarizine have been used commonly in China. Choice is based on efficacy, adverse events, and coexistent conditions. However, most of medications have side effects and contraindication that may limit their use.

Acupuncture, which is one of the main treatment modalities of Traditional Chinese Medicine (TCM), has been used for both the prevention and treatment of diseases for over three thousand years [9]. Although how acupuncture works is still unknown [10], the range of indications of acupuncture (especially for pain management), the variety of different acupuncture methods and the probability that the effects are made up of a specific and a nonspecific component have been acknowledged by more and more western countries [11].

Many studies have already reported encouraging results in the therapy of migraine by acupuncture. In 2001 a systematic review on acupuncture for idiopathic headache had underlined the existing evidence that acupuncture had an effective role in the treatment of patients with migraine [12], but methodological or reporting shortcomings were found in the majority of the studies, so the evidence was insufficient to determine the efficacy of acupuncture compared to medication, or to wait list control or sham acupuncture, in the management of patients with migraine. Since that systematic review, several large, randomized trials on the effectiveness of acupuncture as treatment for migraine prophylaxis have been published in western countries, but there seems to be a lack of high quality randomized controlled trials from China. China is the origin of acupuncture and the country where acupuncture has been used most commonly in clinical practice. Therefore, we are performing a randomized controlled trial to investigate the efficacy of acupuncture compared with flunarizine in patients who have frequent migraine attacks in China.

## Methods

This trial is a multicenter prospective, randomized, controlled clinical trial. The central randomization is performed by Research Center of Clinical Epidemiology Affiliated to Peking University in China, which uses block randomization to generate the random allocation sequence and prepares a predetermined computer-made randomization opaque sealed envelopes. The opaque sealed envelopes are numbered consecutively and were connected into a strain. It is requested that each envelope should be separated from the strain and then be opened in sequence only after baseline period when the patient has been registered in the trial. Patient and assessors are blinded (blinded telephone interviewers) with regard to the acupuncture treatment administered. The trial is executed in the following five hospitals from June 2007 to June 2009: Beijing Traditional Chinese Medicine Hospital Affiliated to Capital Medical University, Peking University Third Hospital, Beijing Tiantan Hospital Affiliated to Capital Medical University, Huguosi Hospital Affiliated to the Beijing University of Chinese Medicine and Dongzhimen Hospital Affiliated to the Beijing University of Chinese Medicine. Physicians who enroll participants and assessors who collect data in these five hospitals must have a 3-day training seminar concerning treatment modalities and trial's documentation prior to the trial to make sure all practices at each of the five hospitals were the same. Periodic check-up contained the coincidence of the practices taken in every hospital.

This trial is performed according to the principles of the Declaration of Helsinki (Version Edinburgh 2000). The trial protocol has been approved by the Research Ethical Committee of Beijing Traditional Chinese Medicine Hospital Affiliated to Capital Medical University on May 2007.

### Participants

One hundred and forty patients with migraine without aura enrolled in the trial are recruited from outpatient in acupuncture clinics of the five hospitals. The main inclusion criteria are: patients suffering from migraine without aura (more than 2 migraine attacks in 4 weeks), diagnosed according to diagnostic criteria of the International Headache Society [1]; male or female; aged 18–65 years; patients who had not used acupuncture or drugs with migraine prophylactic effects within the last 3 months; patients who have given written informed consent.

The main exclusion criteria are: tension-type headache, cluster headache and other primary headaches; secondary headache and other neurological diseases; neuralgia of the face or head; pregnancy, nursing mother or insufficient contraception; use of prophylactic migraine medication in the last 3 months; therapy with β-blocker in the last 3 months; intake of antipsychotic or antidepressant drugs; participation in another clinical trial; having family history of depression, Parkinson disease and other extra-pyramidal diseases.

According to the previous studies in China and our pilot study, we anticipate that the proportion of responders [13] (50% or greater reduction in attack frequency) would be 65% [14,15] in control group and 90% [16] in acupuncture group. Based on 0.9 power to detect a significant difference (α = 0.05, two-sided), 56 patients are required for each group calculated by EpiCalc 2000 Version 1.02. To compensate for dropout patients, we plan to enroll 70 patients per group.

### Procedures

According to predetermined randomization envelopes, 140 eligible patients are randomly allocated to acupuncture group or control group (see Figure 1). The patients have an equal probability of being assigned to either of two groups. Patients need to record headaches and usage of acute medication in headache diary from baseline period to the 16^th ^week after randomization. According to Case Report Form including all outcome measures, endpoints are collected separately 16 weeks after randomization by blinded telephone interviewers in the five hospitals to evaluate the long term effect of acupuncture prophylaxis.

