### Intervention

In addition to rigorous methodological quality, both verum acupuncture and sham acupuncture interventions have been proposed based on a broad literature review and a consensus with acupuncture experts in Beijing Traditional Chinese Medicine Hospital. We conducted a pilot study with sample size 32 per group to confirm the efficacy of verum acupuncture compared with sham acupuncture. Besides, the interventions of two groups are based on the experiences of physicians who had worked with acupuncture for 20 years.

In the acupuncture group, 3 acupuncture sessions per week are carried out and placebo medicine is taken once a night for 4 weeks. In the control group, medicine (flunarizine) once a night for 4 weeks is given and 3 sham-acupuncture sessions are given per week. There are several common approaches of verum/sham acupuncture in both groups including: bilateral points; usage of disposable, sterile steel needles (0.32 mm × 40 mm); 10–12 needles used each time; skin disinfection with 75% alcohol; needles retention for 30 minutes and no moxibustion or electrical stimulation. Patients of both groups received 12 sessions of verum/sham acupuncture in 4 weeks.

The placebo medicines have exactly the same appearance as true medicines (flunarizine). Both Flunarizine and placebo are taken 10 mg once per night for the first 2 weeks and then 5 mg once per night for the next 2 weeks. All patients are allowed to treat acute headaches as need, but the type and dose of acute medications should be recorded in a headache diary.

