### Outcome measures

The efficacy of acupuncture for migraine prophylaxis is assessed by the following primary outcome measures:

1. Change in frequency and duration of migraine attacks [13].

2. The proportion of responders, defined as the proportion of patients with a reduction of migraine days by at least 50% [13].

3. Visual Analogue Scale (VAS) to assess the severity of migraine pain [17].

4. Short-Form of McGill Pain Questionnaire (SF-MPQ) [17,18].

The secondary outcome measures include:

1. The summary scales of the SF-36 [19,20].

2. Intake of acute-medication [13].

3. Number of patients with adverse side effects [21].

4. Change in the frequency of nausea and vomiting [22].

The outcome measures above will be assessed before the treatment, the week of the last acupuncture session and 12 weeks after the last acupuncture session.

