### Statistical analysis

All analyses will be done on the intention-to-treat group of participants who have been randomized regardless of whether they receive any treatment. Missing data will be replaced according to the principle of the last observation carried forward. A variance analysis reject the global hypothesis H_0_: "There is no difference in the success probability between two groups." The significant level used for the statistical analysis is 5%, therefore P < 0.05 indicates significance. Analysis of variance (ANOVA) for repeated measures is used to compare the two groups. Comparisons within groups for the outcomes in each one of the time point were done using the Tukey's post hoc test of Multivariate Analysis of Variance (MANOVA). In the case of proportions, a *chi-square test *is applied. Stratified analysis within five different centers will be performed to control confounding factor if necessary. All analyses are performed using the Statistical Package for the Social Sciences (SPSS) software program (version 13.0) for Windows XP.

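### For the diary outcomes, LOCF on a week-4/week-16 schedule can enter an on-treatment value as the long-term result, although later diary records may exist

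*Protocol article*

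**What the plan says.** All statements are from the protocol article.

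- **Procedures:** "Patients need to record headaches and usage of acute medication in headache diary from baseline period", and the recording continues to the 16th week after randomisation. The late collection is described as "endpoints are collected separately 16 weeks after randomization by blinded telephone interviewers", and its stated purpose is to judge the long-term effect.
- **Outcome measures:** every outcome is assessed "before the treatment, the week of the last acupuncture session and 12 weeks after the last acupuncture session".
- **Intervention:** "Patients of both groups received 12 sessions of verum/sham acupuncture in 4 weeks". The nightly flunarizine or placebo covers the same four weeks.
- **Statistical analysis:** the analysis includes everyone randomised. "Missing data will be replaced according to the principle of the last observation carried forward". "Analysis of variance (ANOVA) for repeated measures is used to compare the two groups", and proportions are compared by chi-square test.
- **Participants:** 56 patients per group are required, and 70 are enrolled to allow for dropout.

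The diary is said to hold headaches and acute medication. The outcomes that depend on it are therefore attack frequency and duration, migraine days (and so responder status) and acute-medication intake. SF-36, SF-MPQ and VAS are not described as diary items.

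**The concern.** The week-16 assessment exists to show whether benefit lasts after treatment stops. The week-4 assessment falls in the last week of needling and of nightly medicine in both arms. If the week-16 value is missing and week 4 is the previous assessment, LOCF enters an on-treatment value as the answer to an off-treatment question. In effect it assumes no waning over 12 weeks in the patients who left.

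For questionnaire outcomes measured only at visits, nothing lies between the two points. For the diary outcomes something may: a patient who records until week 12 and then leaves has eight weeks of off-treatment diary (weeks 5 to 12) that no stated comparison uses. What is at stake is the comparison of persistence between acupuncture and flunarizine on diary-based primary outcomes.

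**Working it through.** **1. Timeline.** Treatment lasts 4 weeks, and the last assessment comes 12 weeks after the last session: 4 + 12 = week 16. This agrees with the week-16 collection under Procedures. The post-baseline assessments are therefore at about weeks 4 and 16, with none between.

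**2. What LOCF does on this schedule.**
- Week 16 missing, week 4 present: the week-4 value is carried 12 weeks.
- Both missing: the baseline value is carried, so the patient counts as a non-responder.

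The persistence problem is the first case.

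**3. The plan's own loss allowance.** With 65% and 90% responders, two-sided alpha 0.05, power 0.90 and no continuity correction, the usual two-proportion formula gives 57 per group, against 56 stated. That is close enough, and it is not disputed here. The allowance is 70 − 56 = 14 per group, and 1 − 56/70 = 0.20. The article does not state the 20% itself, nor when losses are expected.

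**4. Bias in the week-16 responder difference.** In arm g, let f_g be the share of patients whose week-4 value is carried. Let w_g be the waning in those same patients (responder rate at week 4 minus the rate they would have had at week 16). LOCF overstates the arm's week-16 rate by f_g × w_g, so

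bias in (acupuncture − control) = f_A × w_A − f_C × w_C.

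With equal losses f in both arms this becomes f × (w_A − w_C). Differential waning is an assumption, because the article gives no figure for it.

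| Assumed w_A − w_C | f = 0.20 (all 14 of 70 carried from week 4) | f = 0.10 (7 of 70) |
|---|---|---|
| 0 points | 0 | 0 |
| 10 points | 0.20 × 10 = 2 | 0.10 × 10 = 1 |
| 20 points | 0.20 × 20 = 4 | 0.10 × 20 = 2 |
| 30 points | 0.20 × 30 = 6 | 0.10 × 30 = 3 |

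The sign follows the arm that wanes more. If acupuncture wanes more, its advantage is overstated; if flunarizine does, the advantage is understated. For scale, the planned difference is 90 − 65 = 25 points, so 2, 4 and 6 points are 8%, 16% and 24% of it.

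**The case against.** The strongest reply is that this is an ordinary design reported in a condensed article. One assessment at the end of treatment and one at follow-up is common. Counting windows and the handling of intermediate diary data usually belong in a full protocol or analysis plan, which is not shown. The missing windows are indeed no finding. But the assessment points and the LOCF rule are both stated, and the point concerns what those statements do together.

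Other parts of the reply stand and limit the point:

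- **The last observation might mean the last diary entry.** The Statistical analysis section does not exclude that. It does not say it either, and the only schedule given points to week 4.
- **Later diary data may not be in hand.** No diary collection between the end of treatment and week 16 is described. A patient lost at week 10 may never return the diary.
- **Not all 14 losses per arm need fall after week 4.** Those who leave during treatment have no follow-up diary, so f = 0.20 is an upper figure.
- **Only diary outcomes are affected.** For SF-36, and as far as stated SF-MPQ and VAS, the step from week 4 to week 16 is simply the visit schedule.

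A reader might go further and infer that diary weeks 5-12, half the post-randomisation record, are lost. The article does not support this, because it states no counting window; its only 4-week count is an eligibility criterion. The unused share depends on the assumed window:

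- 4-week windows: 8/16 = 50%
- one-week windows: 14/16 = 87.5%
- one window of each length: 11/16 = 69%
- a final point that summarises weeks 5-16: 0%

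A reader might also infer a sizeable loss of precision. At an assumed between-block correlation of 0.6, the mean of four blocks has variance (1 + 3 × 0.6)/4 = 0.70 of a single block, a standard error 16% smaller. That is the wrong comparison. The planned repeated-measures analysis would already use two post-baseline blocks, with variance (1 + 0.6)/2 = 0.80. The ratio is 0.70/0.80 = 0.875, a gain of 6.5% (11% to 3% for correlations 0.4 to 0.8). Even this belongs to a 16-week average. With complete data and an unstructured covariance, extra blocks do not sharpen a weeks 13-16 contrast.

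**Conclusion.** The point holds as a missing-data weakness, limited to the diary outcomes. On the stated schedule, LOCF lets an end-of-treatment value stand for the week-16 off-treatment result in patients lost between the two assessments, while diary records closer to week 16 may exist.

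The bias in the responder difference is about 2, 4 or 6 percentage points under these assumptions: 20% loss in each arm, every loss carried from week 4, and differential waning of 10, 20 or 30 points in those patients. It shrinks in proportion if fewer losses fall after week 4, and is zero if losses and waning are equal in the two arms. Whether waning is equal is what the week-16 comparison is meant to show, so it should not be built in by the missing-data rule.

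This is not a contradiction or an arithmetic error: the sections agree on the timeline and the sample size reproduces. The documents show neither that half the data is lost nor that the standard error would fall by 16%. The change is worth making because it is specific and cheap.

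**What to change.** For attack frequency and duration, migraine days and acute-medication use only:

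1. Summarise the diary in 28-day blocks: weeks 1-4, 5-8, 9-12 and 13-16. State these as the counting windows and put baseline counts on the same 28-day scale.
2. Replace LOCF with a repeated-measures mixed model on the four blocks, with treatment, block and their interaction, and baseline as covariate. Keep weeks 13-16 as the long-term contrast.
3. Let whatever intermediate diary data are retrieved inform missing weeks 13-16 values. Derive responder status for that block from migraine days handled under the same model, so that the two results agree.
4. Ask patients who withdraw to return the diary pages completed so far.

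The cost is some extra diary data entry and a few lines of analysis wording; no patients or visits are added. The limits should be stated. The model assumes that missingness is explained by the recorded data, and the intermediate blocks help only where the diaries of patients who drop out come back. Outcomes not recorded in the diary are outside this change.

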**Figure 1 F1:**
[figure not shown]
**Trial profile**.

### Intervention

In addition to rigorous methodological quality, both verum acupuncture and sham acupuncture interventions have been proposed based on a broad literature review and a consensus with acupuncture experts in Beijing Traditional Chinese Medicine Hospital. We conducted a pilot study with sample size 32 per group to confirm the efficacy of verum acupuncture compared with sham acupuncture. Besides, the interventions of two groups are based on the experiences of physicians who had worked with acupuncture for 20 years.

In the acupuncture group, 3 acupuncture sessions per week are carried out and placebo medicine is taken once a night for 4 weeks. In the control group, medicine (flunarizine) once a night for 4 weeks is given and 3 sham-acupuncture sessions are given per week. There are several common approaches of verum/sham acupuncture in both groups including: bilateral points; usage of disposable, sterile steel needles (0.32 mm × 40 mm); 10–12 needles used each time; skin disinfection with 75% alcohol; needles retention for 30 minutes and no moxibustion or electrical stimulation. Patients of both groups received 12 sessions of verum/sham acupuncture in 4 weeks.

The placebo medicines have exactly the same appearance as true medicines (flunarizine). Both Flunarizine and placebo are taken 10 mg once per night for the first 2 weeks and then 5 mg once per night for the next 2 weeks. All patients are allowed to treat acute headaches as need, but the type and dose of acute medications should be recorded in a headache diary.

#### Verum Acupuncture

The obligatory points used in acupuncture group include DU20 (Baihui), DU24 (Shenting), GB13 (Benshen), GB8 (Shuaigu), SJ20 (Jiaosun) and GB20 (Fengchi). Additional points can be chosen according to syndrome differentiation of meridians (see Figure 2):

